## Methods and Analysis

### For Study Design

The study design and report are according to the methods section of the Strengthening the Reporting of Observational Studies in Epidemiology (STROBE) (22) for cohort studies. The retrospective study used hospital health records and third party databases as the data source and management platform. It is based on the program “evidence-based study of integrated Chinese and Western medicine in metabolic diseases of glycolipids” hosted by the China Academy of Chinese Medical Sciences (project number: 2020YJSZX-4) to develop the risk factors of NODAP. This multicenter, retrospective, cohort study will be carried out between June 2021 and December 2023 in four top hospitals from different districts of China. The recruitment and research sites are 1. Xian Hospital, China Academy of Chinese Medical Sciences, Beijing. 2. Beijing Anshan Hospital, Capital Medical University, Beijing. 3. The First Affiliated Hospital of Guangdong Pharmaceutical University, Guangdong. 4. Affiliated Hospital of Traditional Chinese Medicine of Southwest Medical University, Sichuan. Additional hospital sites may be added based on feasibility and resources available. The study has been registered for clinical trials by the Chinese Clinical Trial Registry (**ChiCTR2100047241**), which provided an overview of our methodology. Through the establishment of validation dataset and training dataset, machine learning is conducted and the prediction model is finally formed. The specific overview of our methodology is shown in Figure 1.

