### Statistical Analysis

Baseline demographic characteristics and study outcomes conforming to normal distribution were expressed as mean ± standard deviation. The *t*-test was used for comparison between the two groups. The measurement data not conforming to normal distribution was represented as the median (quaternary interval), and the comparison between the two groups was performed using the Mann–Whitney *U* test. Descriptive statistics will be used for the overall cohort and aggregated statistics will be calculated. Descriptive statistics are used for the entire queue and the aggregated statistics are calculated. Enumeration data were expressed as frequency or percentage, and χ*2* test was used for comparison between the two groups. Univariate analysis was conducted for all factors first, and statistical learning methods such as tree integration algorithm and Lasso regression were adopted to compare and screen related risk factors from multi-dimensional perspectives. To avoid omission of important variables, covariates with *P* < 0.01 in univariate analysis and important factors screened by statistical learning method were included in multivariate logistic regression analysis. Independent risk factors for NODAP were analyzed by progressive forward regression analysis, and the OR value of each related factor and its 95%CI were estimated. *P* < 0.05 on both sides of all tests indicated statistically significant differences.

We will evaluate the potential predictors of NODAP informed by prior literature (10, 20). The data set will be randomly divided into a training dataset and an internal validation dataset in a 5:5 ratio. We will include all a priori selected variables in the final model; the Bootstrap method was used for model internal validation in this data set. If necessary, non-normally distributed variables will be transformed using the Box-Cox transformation. The validation will be established with the same inclusion and exclusion criteria and sensitivity analyses will be performed. All analyses were performed using R3.6.1 and SPSS^®^ Statistics 21 software (IBM^®^, Armonk, NY, USA). Prism 5 (GraphPad Software Inc., San Diego, CA, USA) is used for drawing statistical graphs.

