### Sample Size

Based on prior studies and conditions of each hospital (31), the number of PCI surgical interventions is between 10,000 and 15,000 in the past 10 years and in which 6.1–11.6% patients (10, 32) may develop NODAP (at least 610 patients). For the exploratory analysis of multiple risk factors, ≥10 events per variable (EPV) are necessary to obtain sufficient degrees of freedom, with the assumption of at least 20 patients with the outcome (NODAP) per predictor variable (33). The ratio of the two groups is set to 5:5 (validation dataset: training dataset); the sample size could be calculated as 300 in both the training set and an internal validation set. The actual sample size may be larger than the calculated amount, thus it will be adjusted according to the situation.

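### A random 5:5 split and a bootstrap are both named for internal validation without being reconciled, and the split withholds half the events from model fitting

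*Protocol article*

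**What the plan says.** In the protocol article, the second paragraph of Statistical Analysis states: "The data set will be randomly divided into a training dataset and an internal validation dataset in a 5:5 ratio". The next sentence adds that "the Bootstrap method was used for model internal validation in this data set". It is not stated whether this means the whole cohort, the training half or the validation half, or which result is the one to report. On the source of the validation set the section says only: "The validation will be established with the same inclusion and exclusion criteria and sensitivity analyses will be performed".

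The Sample Size section repeats the 5:5 ratio and puts each half at 300. It takes as its base that "the number of PCI surgical interventions is between 10,000 and 15,000 in the past 10 years", applies a NODAP rate of 6.1% to 11.6%, and gives at least 610 events. It asks for at least 10 events per variable and assumes at least 20 patients with the outcome per predictor.

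The data come from patients treated "in four top hospitals from different districts of China" (For Study Design). That section allows for more sites but does not set any aside for validation.

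**The concern.** Split-sample validation and bootstrap validation answer the same question, namely how far apparent performance overstates performance in new patients from the same population. Bootstrap answers it with every event used for fitting. The split answers it by fitting on half the events and testing on the other half, so it costs precision twice. The coefficients rest on half the data, and the performance estimate rests on the other half and on one random allocation. Where a plan names both, the analyst can choose afterwards which to report.

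What is at stake is the stability and calibration of the final model, and the precision of the AUC. The Model Evaluation section makes AUC the measure for comparing the candidate models.

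**Working it through.** **Inputs.**
- PCI procedures 10,000 to 15,000, NODAP rate 6.1% to 11.6%, floor of 10 and assumption of 20 events per predictor, 300 per half: Sample Size.
- Candidate variables, counted from Table 2: 5 demographic + 8 history + 12 diagnostic + 3 PCI + 2 medication = 30.
- About 30% of PCI patients have diabetes: Introduction. Patients with diabetes before PCI are not eligible: Table 1. Applying this 30% to the procedure count is my assumption.

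**The plan's own figures.** 10,000 × 0.061 = 610 events, as stated. Half is 305, close to the stated 300. Also 30 × 10 = 300 and (30 × 20)/2 = 300. So 300 reads naturally as events per half, though the text does not say whether it means events or patients.

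**Events per variable (EPV) = events / 30.**

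| Scenario | Events, whole cohort | EPV | Events, training half | EPV |
|---|---|---|---|---|
| 10,000 × 6.1% | 610 | 20.3 | 305 | 10.2 |
| 15,000 × 11.6% | 1,740 | 58.0 | 870 | 29.0 |
| 10,000 × 0.70 × 6.1% (assumed exclusion) | 427 | 14.2 | about 214 | 7.1 |
| 15,000 × 0.70 × 11.6% (assumed exclusion) | 1,218 | 40.6 | 609 | 20.3 |

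At the stated minimum the whole cohort meets the assumed 20 per predictor. The training half does not: 305/20 supports about 15 predictors, half of Table 2. This counts variables, as the plan does. If ACS type takes two parameters and blood pressure is split into systolic and diastolic, there are 32 parameters, and the minimum figures become 610/32 = 19.1 and 305/32 = 9.5.

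**Precision of the held-out AUC (Hanley-McNeil, assumed AUC A = 0.75).** With a = A/(2 − A) = 0.600 and b = 2A²/(1 + A) = 0.643, the variance is [A(1 − A) + (n₁ − 1)(a − A²) + (n₀ − 1)(b − A²)]/(n₁n₀).
- Validation half at the stated minimum, n₁ = 305 and n₀ = 5,000 − 305 = 4,695: SE 0.0165, 95% half-width 1.96 × 0.0165 = 0.032.
- All 610 events, n₀ = 9,390: SE 0.0117, half-width 0.023.
- Validation half after the assumed 30% exclusion, n₁ = 214 and n₀ = 3,500 − 214 = 3,286: half-width 0.039.

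**Size of the loss in the model (illustrative simulation).** Assumed: 10,000 patients, about 6% with events, 30 independent predictors of which 10 are informative, no variable selection, true AUC 0.69, 60 repetitions. Out-of-sample performance:
- Fitted on the whole cohort: AUC 0.680, calibration slope 0.88.
- Fitted on half: AUC 0.672, calibration slope 0.80.

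The difference in AUC is 0.008. The calibration slope moves further from 1 by 0.08.

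**The case against.** The strongest reply is that the plan works as written. On its stated figures the training half holds 305 to 870 events. That is at or above its floor of 10 per variable, and toward the upper end it is above 20. The AUC lost is about 0.01, and a half-width of about 0.03 is usable. The bootstrap may be meant within the training half, with the other half as a final check, and Figure 1, which is not shown, may make this clear. All of this is fair, and it limits the point to inefficiency and an unresolved specification.

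A reader might infer three stronger criticisms that the document does not support.

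- **That screening leaks into the validation half.** The text says "Univariate analysis was conducted for all factors first", but this orders univariate analysis ahead of the tree and Lasso screening in the same sentence, not ahead of the split. The paragraph on prediction speaks of variables chosen in advance. Nothing confines screening to the training data, so leakage is possible, but neither it nor an optimistic AUC is established.
- **That the split breaks the plan's own EPV floor.** Counted by variable on the stated figures, it does not. It does so only under an added assumption, such as the 30% exclusion or the count of 32 parameters.
- **That the plan wrongly claims transportability.** It calls the validation internal and makes no such claim for it. Both halves do come from the same hospitals, so the split says nothing about new ones, but the absence of validation by hospital contradicts nothing in the text.

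**Conclusion.** The point holds as one of efficiency and clarity. Two internal validations are named and not reconciled, and the one that sets the sample size withholds half the events from fitting. At the plan's minimum of 610 events and 30 candidates, this moves the study from meeting its assumption of 20 events per predictor to about half of it. Toward the upper end (870 training events, EPV 29) the shortfall disappears. If known diabetes removes about 30% of procedures, the minimum training EPV is about 7. That figure is conditional, because the document does not say whether its procedure count already allows for this.

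The consequence should not be overstated. The expected loss is about 0.01 in AUC and a modest loss of calibration, both dependent on the effects assumed in the simulation. The change is worth making because whole-cohort development with bootstrap is better on each count and costs little.

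**What to change.** Delete the 5:5 split from Statistical Analysis and Sample Size, and align the references to a validation set in the Abstract and to training and validation datasets in For Study Design. Develop each candidate model on the whole cohort. Report optimism-corrected AUC and calibration from a bootstrap (for example 500 resamples) that repeats imputation, any outcome-based selection, tuning and fitting in every resample. This also removes the doubt about leakage. Restate the sample size as events in the whole cohort against the number of candidate predictors.

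Where events per hospital allow, add leave-one-hospital-out validation as a supplementary check, with results by hospital. The document gives no event counts by hospital, so feasibility has to be checked first.

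The cost is wording and computing time, and there will be no single hold-out validation table. No new data are needed.

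### The plan does not keep predictor selection inside the validation, and contradicts itself on whether the validated model is a priori or data-selected; if data-selected, its AUC may be optimistic

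*Protocol article*

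**What the plan says.** All the relevant text is in the Statistical Analysis section of the protocol article, apart from one sentence in For Study Design.

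- Screening comes first: "Univariate analysis was conducted for all factors first, and statistical learning methods such as tree integration algorithm and Lasso regression were adopted". No dataset is named; the same paragraph also describes summaries for the whole cohort.
- The results feed a regression: "covariates with *P* < 0.01 in univariate analysis and important factors screened by statistical learning method were included in multivariate logistic regression analysis".
- A stepwise step follows: "Independent risk factors for NODAP were analyzed by progressive forward regression analysis", with odds ratios and confidence intervals.
- The next paragraph introduces the split: "The data set will be randomly divided into a training dataset and an internal validation dataset in a 5:5 ratio".
- It then gives a different rule for the model's content: "We will include all a priori selected variables in the final model". After a semicolon, the same sentence gives the bootstrap: "the Bootstrap method was used for model internal validation in this data set".
- For Study Design gives an order of its own: "Through the establishment of validation dataset and training dataset, machine learning is conducted and the prediction model is finally formed".

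The Model Evaluation section names ROC analysis and the AUC as the measure for judging and comparing models.

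**The concern.** Univariate P values, Lasso or tree picks and forward regression all use the outcome to choose variables. If patients in the validation half help to choose the list, that half is no longer independent of the model tested on it. If the bootstrap starts from a list already chosen, it measures the optimism from estimating coefficients but not the optimism from choosing variables. Either way the AUC looks better than it would in new patients. This applies even to a single model, so it is separate from picking the best of several algorithms by AUC.

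The Introduction sets out to build a predictive model and verify that it works. The AUC is the only performance measure named for that, so a reader needs to know whether it includes the cost of selection. As written, the reader also cannot tell whether the validated model is a fixed list or the product of screening.

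**Working it through.** **What the plan's 300 means.** The Sample Size section states that "the number of PCI surgical interventions is between 10,000 and 15,000 in the past 10 years", with a NODAP rate of 6.1% to 11.6%, at least 610 events, and 300 in each half.

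- Lower bound of events: 10,000 × 0.061 = 610, as stated. Per half: 610 / 2 = 305, close to 300.
- Candidates in Table 2: 5 + 8 + 12 + 3 + 2 = 30. At 10 events per variable: 30 × 10 = 300. At the 20 also mentioned: 30 × 20 = 600.
- If 300 meant patients, events per half would be 300 × 0.061 = 18.3 to 300 × 0.116 = 34.8. That is 18.3 / 30 = 0.6 to 34.8 / 30 = 1.2 events per candidate, against the stated minimum of 10.

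The figure therefore fits events. The text does not say so, and both readings are carried below.

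**Simulations.** The protocol gives no AUC or effect sizes, so these are assumptions.

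- Simulation A: 30 candidates, 8 with real effects, forward selection at P < 0.05 only.
- Simulation B: 30 independent normal candidates; screen at P < 0.01 plus the top five by univariate score (a stand-in for Lasso and tree picks); then forward selection at P < 0.05. True log odds ratios per SD: 0.6, 0.4, 0.3, 0.2, 0.15, 0.1 (moderate); 0.3, 0.2, 0.15 (weak); none (null). True AUC is taken in 60,000 new patients. There were 40 replicates for 10,000 patients and 150 for 600.

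Bias = reported AUC − AUC in new patients. Simulation B gives:

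| Procedure | 10,000 patients, about 305 events per half: moderate / weak / null | 300 patients per half |
|---|---|---|
| Select on all data, test on one half | +0.007 / +0.006 / +0.025 | +0.042 to +0.099 with signal; +0.114 null (6.1%) |
| Select in training half, test on the other | +0.005 / −0.002 / +0.004 | −0.007 to +0.003 |
| Bootstrap in training half, selected list fixed | +0.003 / +0.011 / +0.042 | +0.083 to +0.172 |
| Bootstrap in training half, selection repeated | −0.007 / −0.011 / 0.000 | +0.006 to +0.050 |

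Simulation A agrees on the split: inflation of 0.005 at 610 events in total (0.025 if nothing predicts), and 0.055 to 0.085 for 600 patients in total.

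On the bootstrap, Simulation A gives:

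- 305 events in 5,000 patients: true optimism 0.019. The fixed-list bootstrap finds 0.007, missing 0.019 − 0.007 = 0.012. Repeating selection finds 0.024.
- 300 patients, 35 events: true optimism 0.123. The fixed-list bootstrap finds 0.020, missing 0.123 − 0.020 = 0.103. Repeating selection finds 0.122.

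**If the a priori sentence is followed.** With all 30 variables fitted and no selection, the validation-half AUC in Simulation B is within about 0.01 of the truth in every completed scenario.

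**Precision.** At 10,000 patients the standard error of the all-data bias is 0.002 to 0.003. In the moderate scenario, +0.007 with the leak is hardly distinguishable from +0.005 without it. The null run with 300 patients per half at 11.6% did not finish. The figures show order of magnitude only.

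**The case against.** The strongest reply is that the text never says selection uses the whole cohort. The bootstrap clause shares its sentence with the rule that the a priori variables form the final model; taken literally, no selection remains to be repeated. The Introduction separates exploring risk factors from building a prediction model, so the screening paragraph may serve only the first aim, where a full-cohort analysis is legitimate. For Study Design puts the datasets before the machine learning, and Lasso and tree screening can be read as part of that learning. If selection is confined to the training half, the held-out AUC is about unbiased however the bootstrap is run. Finally, an article may leave resampling detail to an analysis plan.

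Much of this stands. A reader might infer that selection certainly lies outside the validation and that the AUC is bound to be too high. The documents do not support that: the dataset for screening is unstated, and two sentences lean the other way.

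It does not dispose of the point. The For Study Design sentence does not mention the univariate screen or the forward step. The a priori rule conflicts with the data-driven route in the same section and does not settle which one yields the validated model. Nor is this only missing detail: the article fixes thresholds, algorithms, split and bootstrap, in an order that, followed as written, selects first and validates afterwards.

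**Conclusion.** The point holds conditionally and should be fixed. The Statistical Analysis section contradicts itself on whether the validated model is a priori or data-selected, and it does not confine selection to the training half or build it into the bootstrap. Optimism follows only if the data-selected model is the one validated and selection either uses all data or is held fixed across resamples.

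On the reading of 300 that matches the plan's own arithmetic (events), the split leak is small with real signal, about 0.005 to 0.007. The 0.025 figure needs no candidate to predict at all, which is unlikely: the Abstract already names impaired glucose tolerance and age as risk factors, and Table 2 contains fasting glucose and HbA1c. The range of about 0.04 to 0.10 requires 300 to mean patients, which conflicts with the stated events per variable. It would therefore be wrong to present the large figures as the expected size. A fixed-list bootstrap understates optimism under either reading. All sizes rest on assumed effects; Simulation B also assumes independent predictors and uses few replicates.

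**What to change.** State in the Statistical Analysis section whether the final prediction model is a priori or data-selected, and remove or reword the other statement.

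If it is a priori, list the variables and say that the screening results do not alter the list.

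If it is data-selected, say that univariate screening, Lasso and tree screening, forward selection and any outcome-informed preprocessing are run in the training half only. Say also that each bootstrap resample repeats all of these steps from the full Table 2 list, and report the optimism-corrected AUC from that procedure.

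The full-cohort odds-ratio analysis of risk factors can stay, provided it does not choose the variables of the validated model.

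The change takes two or three sentences. It costs more computing time, and the reported AUC will probably be slightly lower.

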### Sample Size

Based on prior studies and conditions of each hospital (31), the number of PCI surgical interventions is between 10,000 and 15,000 in the past 10 years and in which 6.1–11.6% patients (10, 32) may develop NODAP (at least 610 patients). For the exploratory analysis of multiple risk factors, ≥10 events per variable (EPV) are necessary to obtain sufficient degrees of freedom, with the assumption of at least 20 patients with the outcome (NODAP) per predictor variable (33). The ratio of the two groups is set to 5:5 (validation dataset: training dataset); the sample size could be calculated as 300 in both the training set and an internal validation set. The actual sample size may be larger than the calculated amount, thus it will be adjusted according to the situation.

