## Introduction

Type 2 Diabetes mellitus (T2DM) is a major health concern worldwide, with a prevalence of about 463 million by 2019, and a 62% increase since 2009 (1). In Chinese adults, the estimated T2DM and pre-T2DM prevalence are 10.9% and 35.7% (2), respectively. It is a strong risk factor for cardiovascular artery disease (CAD) and major adverse cardiovascular events (MACE) (3–5). A pooled analysis involving more than 1 million participants in Asia found that patients with T2DM had a higher risk (hazard ratio, 1.89) of all-cause death than those without T2DM (6). People are conferred an eight fold increase in death risk by unrecognized myocardial infarction (MI) with diabetes (7). As patients with acute ST-segment elevation myocardial infarction (STEMI) significantly improved after percutaneous coronary intervention (PCI), the 10-year survival rate was nearly 76% (8). Prolonged life expectancy makes chronic care management after PCI a concern. Nearly half of the inpatients with MI complicated with T2DM (9, 10) and good blood glucose control is one of the keys. There have been multiple studies regarding clinical outcomes in patients after PCI with known T2DM (11, 12). Patients after PCI with chronic T2DM emerge with poor clinical outcomes and different treatment strategies (13, 14). Patients approximately 30% who underwent PCI suffer from diabetes (13). Considering the counter-balancing effects of hemorrhagic and ischemic complications, the recent ultra-short DAPT strategy may not be suitable for patients with T2DM (15). New-onset of diabetes after PCI (NODAP) has attracted much attention; a 5-year survival of patients after revascularization with diabetes were worse (16). Among 3,683 acute coronary syndrome (ACS) patients (without T2DM before PCI), 436 patients (11.8%) developed NODAP after a follow-up of 3.41 ± .9 years (10).

However, the risk factors and pathophysiological mechanisms for NODAP remain unknown. The risk factors for NODAP may be different from those for simple diabetes. Patients after PCI are generally elderly, and are associated with a variety of metabolic diseases (obesity, hyperlipidemia, etc.) and stress states related to surgery; all the above predict the risk of T2DM. Previous studies show that abnormal heart rate variability is a risk factor for diabetes (17), and heart rate variability (low SDNN) is common in patients undergoing PCI (18). High intensity statins (19, 20) also has adverse effects on diabetes.

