**Inclusion criteria**	
i	Age > 18 years
ii	Adults with a primary diagnosis of an ACS (23)
iii	Did not meet the diagnostic criteria for diabetes (24, 25) before the PCI surgery^*^, no history of taking hypoglycemic drugs or insulin
iv	Only have received the initial PCI
v	outpatient follow-up ≥12 months
vi	Volunteer to participate in the study

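### The stated minimum of 610 NODAP cases applies the lowest rate to all PCI procedures; on the protocol's own diabetes share it falls to about 427, so 610 is not a minimum

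*Protocol article*

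**What the plan says.** The Sample Size section of the protocol article takes its volume from procedures: "the number of PCI surgical interventions is between 10,000 and 15,000 in the past 10 years". It then applies a range of rates: "in which 6.1–11.6% patients (10, 32) may develop NODAP (at least 610 patients". It asks for at least 10 events per variable and assumes at least 20 patients with the outcome per predictor. It splits the data 5:5 and arrives at 300 in each of the training and internal validation sets.

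Three other statements bear on the denominator:

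- The Introduction says: "Patients approximately 30% who underwent PCI suffer from diabetes".
- The Introduction describes the population of reference 10, one of the two sources cited for the rate: "Among 3,683 acute coronary syndrome (ACS) patients (without T2DM before PCI), 436 patients (11.8%) developed NODAP".
- Table 1 admits only ACS patients who did not meet diabetes criteria before PCI, have at least 12 months of outpatient follow-up, and satisfy "Only have received the initial PCI". It excludes patients with CABG, several comorbidities, or no secondary prevention (at least aspirin, a P2Y12 inhibitor and a statin).

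**The concern.** New-onset diabetes can occur only in someone who does not already have diabetes. The Sample Size section multiplies a new-onset rate by a count of procedures that, on the article's own account, includes a substantial share of patients with diabetes. It also includes any repeat procedures, non-ACS indications and patients with short follow-up. The result is then labelled a minimum.

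This matters because 610 is the only event count in the article and its margin is thin. Two halves of 300 events need 600, and 610 leaves 10 to spare, so a loss of more than 1.6% (10/610) removes the margin. If the event supply is smaller, the training half cannot carry the Table 2 candidates at the plan's own floor of 10 events each. The Statistical Analysis section screens all factors and keeps all a priori selected variables in the final model, so the number of candidates is not a side issue.

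**Working it through.** **Inputs**

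- Procedures: 10,000 to 15,000 (Sample Size).
- Rate: 6.1% to 11.6% (Sample Size).
- Share of PCI patients with diabetes: about 30% (Introduction).
- Floor of 10 events per variable, and 20 events per predictor assumed (Sample Size).
- Candidate items in Table 2, counting one per listed item: 5 demographic + 8 history + 12 diagnostic + 3 PCI-related + 2 medication = 30. This is a tally, not a figure the article states. It ignores extra parameters for multi-level factors.

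**Step 1: reproduce the stated figure.** Minimum procedures x lowest rate = 10,000 x 0.061 = 610. The match is exact, so no deduction was made.

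**Step 2: remove only patients with diabetes.** Events = procedures x (1 - diabetes share) x rate = 10,000 x 0.70 x 0.061 = 427. The loss is 610 - 427 = 183, and 183/610 = 30%. On the other base, 610/427 = 1.43, so 610 is 43% above the corrected figure.

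**Step 3: events per variable in a 5:5 split, over 30 items**

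| Total events | Per half | Events per variable | Predictors at 10 each | Predictors at 20 each |
|---|---|---|---|---|
| 610 | 305 | 10.2 | 30 | 15 |
| 427 | 213.5 | 7.1 | 21 | 10 |

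At 20 events each, 30 items need 600 events in the training half alone. That is not met even with 305, so this shortfall exists before any correction. What the correction changes is the floor of 10, which goes from just met to missed.

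**Step 4: the rest of the plan's range, after the same 30% deduction**

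- 15,000 procedures at 6.1%: 15,000 x 0.70 x 0.061 = 640.5.
- 10,000 procedures at 11.6%: 10,000 x 0.70 x 0.116 = 812.
- Break-even for 610: 10,000/0.70 = about 14,286 procedures at 6.1%, or 610/7,000 = 8.7% at 10,000 procedures.

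**Step 5: sensitivity to the diabetes share.** The Introduction also says "Nearly half of the inpatients with MI complicated with T2DM (9, 10". That concerns inpatients with MI, not all PCI patients, so it serves only as an upper value: 10,000 x 0.50 x 0.061 = 305 events, 152.5 per half, 5.1 per variable.

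**Step 6: the remaining criteria.** ACS only, first PCI only, 12 months of follow-up, secondary prevention and the comorbidity exclusions all shrink the denominator. The documents give no fractions for them. Purely as an illustration, assume that 70% to 85% of procedures are for ACS, that 50% to 80% of patients have the required follow-up, and that these fractions multiply:

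- Low: 7,000 x 0.70 x 0.50 x 0.061 = 149.
- High: 7,000 x 0.85 x 0.80 x 0.061 = 290.

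These fractions are assumptions, and the conclusion does not rest on them.

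**The case against.** The strongest reply is that the arithmetic is right and that 610 may still be reached. Both points stand. At the upper volume or the upper rate the corrected count exceeds 610. A reader might therefore go too far in inferring that the study cannot support its predictors; the documents show only that the stated minimum is not a minimum.

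Other points also limit the claim:

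- The article describes the population for reference 10 only, whose 11.8% lies near the upper end of the range. It does not describe the population behind the 6.1%. That this is a rate among patients without diabetes is the natural reading, because only they are at risk, but it is an inference.
- A reader might infer that 300 per set is 610 divided by two. The article does not say so: 30 x 10 and 15 x 20 also give 300. Nor does it make clear whether 300 counts events or patients.
- A reader might convert the 11.8% over about 3.4 years in the Introduction into a one-year risk and lower the count again. That needs a constant hazard, which conflicts with the statement under Outcomes Measures that onset is mainly within one year. It also treats the 12-month minimum as typical follow-up, which the documents do not support.
- The 30% is approximate and comes from a cited source, not from the four sites.

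Some replies do not repair the figure. Reading interventions as patients leaves the diabetes share in place. The last sentence of Sample Size allows adjustment, but the departure it names is a sample larger than calculated. The option of adding sites, under Study Design, may raise the eventual count but does not make 610 a minimum for the volume stated. In the Data section a number appears to be missing where the expected count of eligible patients would stand. It may have been lost in the text, so nothing is held against the plan for it, but it does not alter how 610 was obtained.

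**Conclusion.** The concern holds for the claimed minimum. At the plan's lowest volume and lowest rate, its own diabetes share brings 610 down to about 427 events, or about 213 per half. That is about 7 events per variable over roughly 30 items, against a stated floor of 10. The result rests on three things: the approximate 30%, a 6.1% rate that applies to patients without diabetes, and one parameter per Table 2 item. The remaining eligibility criteria push the count lower by an unknown amount. The documents do not establish that the study will fall short of 610, nor how far below 427 the true lower end lies. Because 610 is a stated figure that conflicts with the article's own Introduction and Table 1, this is not a detail left to a fuller document.

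**What to change.** 1. Run a count query in the hospital information systems of the four sites, stepping from procedures to patients with a first PCI, to ACS, to no diabetes at baseline, to the remaining Table 1 criteria.
2. Replace the 610 minimum with an event range computed from that eligible count, and state which population each rate describes.
3. State whether 300 per set means events or patients. If it means patients, 6.1% to 11.6% of 300 is only about 18 to 35 events per set.
4. Limit the candidate predictors to what the lower end of the range supports in the training half at the stated events per variable, and say which of 10 or 20 governs.

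The cost is a count query and some restated text, best done before model building. No extra patients are needed. The price is a less favourable stated event count and possibly a shorter predictor list.
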